### Outcome measures of physical activity and mobility

The primary outcome of this study is PA and sedentary time measured with a 3-dimensional accelerometer (Hookie AM20 Activity Meter, Hookie Technologies Ltd., Espoo, Finland and UKK RM42, UKK Institute, Tampere, Finland). The accelerometer is attached on the non-affected anterior thigh line with a transparent, adhesive film as typically used in wound healing (Opsite Flexigrid, Smith&Nephew, United Kingdom). Data are collected over six consecutive days. In the analyses, the crude accelerometer data are used for calculating the parameter of interest. Sedentary behavior (time spent still without moving, MAD <0.0167 g) is assessed from the raw acceleration data based on intensity. The intensity of PA is calculated as one-minute ranges of movement measuring an average of MAD of the resultant acceleration and converted into metabolic equivalents (MET). Using METS, PA is classified into light, moderate and vigorous PA. MAD-based cut-points for light, moderate and vigorous locomotion against VO_2_ across a range of walking speeds are validated in our treadmill tests. In addition to accelerometer measurements, the participants keep PA diary on data collection days.

Level of PA over the previous month is assessed with the self-report scale by Grimby [22], which has been translated into Finnish and further modified and validated [23, 24]. The 7-point scale describes the level of PA as follows: 0) mostly resting, or lying down, 1) hardly any activity, mostly sitting, 2) light physical activity, such as light household tasks, 3) moderate physical activity for about 3 h a week: walking longer distances, cycling and domestic work, 4) moderate physical activity for at least 4 h a week or heavier physical activity 1–2 h a week, 5) heavier physical activity or moderate exercise for at least 3 h a week, and 6) competitive sports. Self-reported PA is assessed at 12 months in addition to the baseline, 3- and 6- month measurement points.

Mobility is measured using the Short Physical Performance Battery (SPPB). The SPPB evaluates balance, mobility and muscle strength by examining an individual’s ability to stand in different positions, time taken to walk 4 m, and time taken to rise from and sit down on a chair 5 times. Each test is scored between 0 and 4, yielding a maximum score of 12. The SPPB is a validated and frequently used tool in older people, with low SPPB sum scores predicting falls, loss of independence and mortality [25].

Perceived difficulties in mobility (in walking outdoors, in walking 2 km and 500 m, climbing up 1 flight of stairs) are assessed using a structured questionnaire with the following response categories: 1) able without difficulty, 2) able with some difficulty, 3) able with a great deal of difficulty, 4) unable without the help of another person, and 5) unable to manage even with help. We assess self-rated mobility by asking “How would you describe your mobility?” using a 4-point scale (very good, good, poor or very poor). The use of an assistive device for mobility is rated for seven listed assistive devices with the response options: 1) no, 2) yes, only indoors, 3) yes, only outdoors, and 4) yes, both indoors and outdoors.

### Secondary outcomes

Life space mobility is measured using the University of Alabama at Birmingham Study of Aging Life Space Assessment, LSA [26]. The LSA comprises 15 items and assesses mobility through the different life-space levels (distance), which the participant reports having moved through during the four weeks preceding the assessment. For each life-space level (bedroom, other rooms, outside home, neighborhood, town, beyond town), participants are asked how many days a week they attained the level and whether they needed help from another person or from assistive devices. Scores range from 0 to 120 with higher scores indicating a larger life-space. Life-space one-month prior to hospital admission is assessed retrospectively during hospitalization. We also ask participants about their life-space mobility during the two weeks immediately following discharge from hospital. We want to evaluate life space shortly after returning home but we do not want to burden our participants with an additional questionnaire or home visit at one month after their hospital discharge. During the measurements at 3 months, after the 6-month intervention, and at the 12-month follow-up, the original 4-week period preceding the assessment is used in the life-space assessment questionnaire.

The Impact on Participation and Autonomy (IPA) questionnaire [27] is a validated questionnaire designed to assess perceived autonomy and participation in various clinical populations, including older people. It consists of five domains: social relations, autonomy in self-care, autonomy outdoors, family role, and work and educational opportunities. The response categories range from 0 (very good) to 4 (very poor). A sum score is calculated, with a higher score indicating more restrictions in participation.

Fear of falling is assessed by Fall Efficacy Scale International (FES-I) [28]. Sixteen questions on concerns about the falling when performing different activities are scored on a 4-point scale ranging from “not at all concerned” to “very concerned”. The scores are added up to calculate a total score that ranges from 16 to 64. A higher score indicates a greater fear of falling. Information on falls (“Have you fallen or slipped during the previous year/previous three months?” yes/no) and injurious falls (“If yes, how many times did you need to be treated by a doctor?”) is also collected.

Disturbing musculoskeletal pain in the low back, hip, knee, ankle and foot is assessed by a questionnaire. Musculoskeletal pain is assessed with the question "Have you suffered from pain in the low back, hip, knee, ankle or foot region daily during the preceding month? Has the pain compromised your mobility?" The three alternative response options are: 1) no; 2) yes, but the pain does not limit my mobility; and 3) yes, the pain limits my mobility. We assess also assess the impact of pain on daily function using the Pain Interference Subscale from the Brief Pain Inventory (BPI) questionnaire [29]. Participants are asked to rate on a scale from 0 to 10 the extent to which pain has interfered with their general activity, mood, walking ability, normal work, relations with other people, sleep and enjoyment of life during the past 24 h. Grip strength of the dominant hand is measured at baseline and at the 6-month follow-up using a Jamar digital hand dynamometer in the sitting position with the elbow in 90 ° flexion close to the body.

### Barriers and facilitators to physical activity

The questionnaire on barriers to PA comprises 17 items under the themes of poor health, fear and negative experiences, lack of knowledge, lack of time and interest, lack of company and unsuitable environment [30]. Each item is rated as yes or no. Barriers and facilitators to mobility in the outdoor (PENBOM and PENFOM) and entrance environments of the home are examined as perceived by the participants, using standardized questionnaires developed in earlier studies [31, 32]. Three months after hospital discharge, environmental features hindering and facilitating outdoor mobility reported by participants will be located on a map using cloud-based Maptionnaire software (Mapita LTD, Helsinki, Finland).

### Review of medical data and health status and demographics

Data on age, gender, marital status, living conditions and education are collected. Self-reported height and weight are recorded and a question about unintentional weight loss of five kg or more is included in the questionnaire. When possible, weight is measured using a standard procedure at the health center hospital. Body mass index is calculated as weight (kg)/height × meters^2^. Perceived sensory functions (vision and hearing) are assessed using a structured questionnaire. At baseline, cognitive status is assessed by the Consortium to Establish a Registry for Alzheimer’s Disease (CERAD) neuropsychological battery [33], which includes a Mini Mental State Examination (MMSE) [34], Executive functions are assessed by Trail Making Tests A and B [35] at baseline and six-month follow-up. Depressive symptoms are measured by the Center for Epidemiological Studies-Depression Scale (CES-D) [36] at baseline and at 3, 6 and 12 months after baseline. Self-rated health is evaluated by the question “How would you describe your health?” using a 4-point scale (very good, good, poor or very poor).

Information on use of formal and informal care and form of dwelling is collected by a questionnaire. At the end of the study, we will the collect information on the stay in hospital and use of formal care from the registers of the health center hospital and national register on the use of health and social services.

### Standard care

At three months after hospital discharge, all participants are interviewed with structured questions on advice, recommendations and possible planned programs concerning the rehabilitation they received post discharge. Typically, older people receive written information on home exercises and safe walking and instructions on how to rise from a chair from a physiotherapist in the hospital ward before discharge to home. Half of the participants will have received standard care alone (control group).

### ProPA intervention

The ProPA intervention study includes a multi-component home rehabilitation intervention program and standard care. The ProPA intervention is an individually tailored 6-month PA and rehabilitation program aimed at promoting physical activity and restoring mobility after hospital discharge. A detailed description of the rehabilitation program is presented in Table 2. The idea for the program arose from the OTAGO Exercise Program designed to prevent falls in older people [37] and ProMo, a previous randomized controlled trial [38] that was successful in restoring mobility [18] and physical activity [19] among community-dwelling older people with a recent hip fracture.

**Table 2 Tab2:** Flow and content of Propa intervention

	Aim	Intervention content	Method
1. Home visit (week 1)	Introduction to the rehabilitation program, duration, GAS method and aims of the study	Current health status, chronic diseases, falls, living environment and use of a walking aid are evaluated. Goal setting is initiated	Interview, information on paper form is given on helping aids, hip pants, shoes and ancillary equipment
2. Home visit (week 2)	Muscle strength program	Individual exercise program to be implemented according to the OTAGO protocol (strength, balance, functional training)	Exercise training, counseling
3. Home visit (week 3)	Functional exercise program (e.g. walking, climbing stairs). Goals of rehabilitation are assessed to fit the participant’s current situation	Individual exercise program to enhance functional capacity and independent ADL functions. Advice for non-medical solutions to increase pain-management skills	Exercise training, interview, counseling
4. Home visit (week 4)	Balance program with progressive balance movements on an individual level (with help of ancillary equipment if needed)	Individual exercise program to increase and maintain balance and agility	Exercise training, goal updating, counseling
1. Call (week 6)	Encouragement to pursue goals and information given if needed	Evaluation of current situation, progress with the training program and their health status	Counseling goal updating
5. Home visit (week 8)	Functional training and progression on each program. Light resistance band training.	Training program is evaluated to fit the participant’s current situation.	Exercise training, interview, goal setting
2. Call (week 10)	Encouragement to pursue goals and information given if needed	Participants are asked about their current situation, progress with the training program and their health status	Counseling
6. Home visit (week 12)	Possibility to train outside of the participants home, e.g., communal gym, swimming pool, elderly exercise group or home-based medium resistance band training	Physical activity counselling, goal setting	Exercise training, counseling, motivational interview to discover new training possibilities
3. Call (week 16)	Encouragement to pursue goals and information given if needed	Evaluation of current situation, progress with the training program and their health status	Counseling
7. Home visit (week 20)	Evaluation of rehabilitation period and plan for future	The success of the goals set beforehand are appraised and new goals set for the future. Evaluation of the physical activity plan. Motivation to continue physically active lifestyle	Counseling

Within two weeks from randomization, a physical therapist initiates the intervention in the participant’s home. The rehabilitation program includes seven home visits, a home exercise program according to the OTAGO protocol, and three phone calls by a physiotherapist. The home visits are targeted for weeks 1, 2, 3, 4, 8 12 and 20, week1 being the start of the rehabilitation program. Booster phone calls to reinforce adherence to the home exercise regimen and physical activity recommendations are targeted for weeks 6, 10 and 16. The participant goes through the OTAGO home exercise program together with the physiotherapist and, in addition, receives instructions in writing. The program, with accompanying illustrations, has been described in more detail earlier [39]. The program is to be performed three times a week. It includes strengthening exercises for the lower limb muscles, balance training, and walking exercises and will be upgraded 4 to 5 times. Progression of the strengthening exercises is implemented with resistance bands. All participants keep an exercise diary on the exercise program during the intervention.

#### Physical activity counseling

Goal Attainment Scaling (GAS) [40] is applied to set one or more PA-related goals. During the first visit, the method is presented to the participants. Their own goals and wishes are discussed to enable them to set goals based on the SMART principle (specific, measurable, achievable, realistic and time-based) [41].

Individual face-to-face PA counseling with a personalized PA plan takes place after three months in the participants’ homes. Motivational interviewing techniques will have been used during the counseling sessions to help participants to find inner motivation for adopting an active lifestyle, overcome barriers and detect sedentary behavior patterns. The topics covered during the session include the participant’s earlier and present PA level, the participant’s interest in returning to her or his previous activities, the possibility to starting a new type of PA or exercise, and guidance on how to be active in performing everyday chores. The problem-solving method is used to address perceived obstacles to PA. Participants are also given information on the PA courses and facilities offered by the municipality. To practice the exercise program, they are also given an opportunity to visit a gym or swimming pool with the physiotherapist.

### Statistical analysis

All analyses will be performed using the intention-to-treat principle. Means, standard deviations and frequencies will be calculated for the demographic variables. Normality of the distributions will be tested. At baseline, the significance of differences between the intervention and control group will be tested by cross-tabulation and chi-square tests in the case of discrete variables, by Student’s t-test for independent samples for normally distributed data and by Mann-Whitney U-test for non-normally distributed continuous data. Associations between variables will be analyzed using Pearson’s correlation coefficient. The effects of the intervention will be assessed using repeated measures ANOVA, covariance analysis and linear mixed models. Generalized estimating equations (GEE) models will be used to analyze differences in changes in prevalence over three time points. The level of statistical significance will be set at *p* < 0.05 (two-sided). In all future publications, data will be reported following the criteria recommended by the CONSORT guidelines [42].

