**Methods:**

Men and women aged 60 years or older hospitalized due to a musculoskeletal injury or disorder in the back or lower limbs are recruited. After discharge from hospital to home, participants are randomized into a six-month ProPA program or a standard care (control) group. The ProPA program consists of a motivational interview, goal attainment process, guidance for safe walking, a progressive home exercise program and physical activity counseling. In addition, frail participants who are not able to go outdoors alone receive support from volunteers.

Primary outcomes are PA measured using a 3-dimentional accelerometer, and mobility assessed by the Short Physical Performance Battery and self-reports. Secondary outcomes are life space mobility, participation restriction, fear of falling, pain, mood, and grip strength. Information on barriers to and enablers of PA participation are also collected. Data on mortality and use of health services are collected from the national register. In this 6-month intervention, all participants are assessed in their homes at baseline and after three and six months, and at 12 months after randomization they will receive a follow-up questionnaire.

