### Design

This study is a parallel group randomized controlled trial (RCT, ISRCTN13461584) with two groups: a promotion of physical activity (ProPA, intervention) group and a standard care (control) group. Figure 1 provides an overview of the study design. Recruitment started during spring 2016 and will be finished by the end of August 2017. After the baseline measurements, participants are randomized into the two study groups. The computer-generated randomization is performed by an independent statistician. Randomization by sex, age (60 to 84 years or 85 years of age and over) and baseline gait speed (< 0.4 m/s or ≥0.4 m/s) is performed in blocks of 10 participants.

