**Fig. 1 Fig1:**

RCT schedule for randomization, measurements and follow-up

All participants are measured three times at home: at baseline immediately after discharge from hospital, and at three and six months thereafter. Moreover, participants are followed up for a further six months (up to 12 months from baseline) to collect data on PA, mobility limitations, life-space mobility, fear of falling, pain and mood.

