### Sample size calculation

A priori sampled size calculations are based on previously published work [20] and on our pilot study conducted among 55 community-dwelling older people who were followed up for six months after discharge from hospital. In our pilot study, using an accelerometer, daily active time measured as mean amplitude deviation (MAD) above 0.0167 g was 250 ± 103 min. It has been estimated that a 20% increase in habitual physical activity, as measured by an accelerometer, in the intervention group compared to standard care control group will be clinically meaningful [21]. For this effect size, a significance level of 0.05 for the PA outcomes and a power of 80% will be set. Thus, the required sample size is 53 participants in each group. Assuming a dropout rate of 10–15%, 60 participants per group (total 120 participants) are required.

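### The GEE contrast for the prevalence outcomes, arm differences in change from a pre-randomization baseline, is valid but gives up power that a common or adjusted baseline would keep

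*Protocol article*

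**What the plan says.** The Statistical analysis section assigns GEE to outcomes expressed as prevalences and names the contrast: "Generalized estimating equations (GEE) models will be used to analyze differences in changes in prevalence over three time points". It gives no link function or model terms and does not say how baseline enters. The sentence before it lists repeated measures ANOVA, covariance analysis and linear mixed models for intervention effects in general, without tying covariance analysis to the GEE.

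The Design section gives the visit schedule, "All participants are measured three times at home: at baseline immediately after discharge from hospital, and at three and six months thereafter", and the order of events: "After the baseline measurements, participants are randomized into the two study groups".

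The likely GEE outcomes are the self-reported mobility items. The abstract counts among the primary outcomes "mobility assessed by the Short Physical Performance Battery and self-reports", and Table 1 lists the mobility-disability items and self-rated mobility under main outcome measures. The outcome section, by contrast, gives accelerometer activity and sedentary time as the primary outcome, and the Discussion names the accelerometer measures and the SPPB.

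**The concern.** A difference in change is normally fitted as an arm-by-time interaction with a free arm term at baseline. The 6-month effect is then the 6-month arm difference minus the observed baseline arm difference. Because randomization follows baseline, the second quantity is an estimate of zero. Subtracting it in full removes no bias and brings its sampling error into the result. A chance baseline imbalance is also over-corrected, because a full change score is used where partial adjustment is efficient.

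On the logit scale the cost grows as baseline prevalence nears 0% or 100%. That matters here: participants have just left hospital after a lower-limb or back problem, so difficulty walking 500 m or 2 km, or climbing stairs, may be close to universal at baseline. The sample size was set for accelerometer active time and no power is stated for these items, so an avoidable loss could hide a real benefit.

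**Working it through.** **The plan's own figure.** There is none for the prevalence outcomes. The only sample size is 53 per group for active time (mean 250, SD 103 min, 20% = 50 min). The formula 2(103/50)²(z_α + z_β)² gives 2 × 4.2436 × (1.645 + 0.842)² = 52.5, so 53, with one-sided α. With two-sided α it gives 2 × 4.2436 × (1.960 + 0.842)² = 66.6, so 67. That mismatch with the two-sided level in Statistical analysis is a separate matter. Here 53 serves only as the evaluable number per arm.

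**Inputs.** From the article: 53 per arm, two-sided 5%, visits at baseline, 3 and 6 months, baseline before randomization. Assumed: 6-month difficulty 70% control v 45% intervention, a range of baseline prevalences and within-person correlations, and logit or identity link.

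**Formulas.** Let d0 and d6 be the arm differences at baseline and 6 months on the link scale, with variances V00 and V66 and covariance V60.
- Difference in change: d6 − d0, variance V66 + V00 − 2·V60.
- Common baseline: d6 − (V60/V00)·d0, variance V66 − V60²/V00.

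Both have expectation δ, the true 6-month difference, because E(d0) = 0. With equal variances and correlation r, the variance ratio is 2(1 − r)/(1 − r²) = 2/(1 + r). If the adjusted test has 80% power, the change test has 61.7% at r = 0.3, 67.9% at r = 0.5 and 73.3% at r = 0.7.

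**Worked case, logit link, baseline 80%, phi 0.3.**
- δ = ln(0.70/0.30) − ln(0.45/0.55) = 1.048
- V66 = 1/(53 × 0.21) + 1/(53 × 0.2475) = 0.1661
- V00 = 2/(53 × 0.16) = 0.2358
- V60 = 0.3/(53√(0.16 × 0.21)) + 0.3/(53√(0.16 × 0.2475)) = 0.0593
- Change: variance 0.2833, SE 0.532, z = 1.97, power Φ(1.97 − 1.96), about 50%
- Common baseline: variance 0.1512, SE 0.389, z = 2.70, power about 77%
- 6-month difference alone: SE √0.1661 = 0.408, z = 2.57, power about 73%

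**Same case, identity link.**
- δ = 0.25, V66 = (0.21 + 0.2475)/53 = 0.00863, V00 = 2 × 0.16/53 = 0.00604
- V60 = 0.3(√(0.16 × 0.21) + √(0.16 × 0.2475))/53 = 0.00216
- Change: variance 0.0103, z = 2.46, power about 69%
- Common baseline: variance 0.00786, z = 2.82, power about 80%

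**Simulation, logit link, 70% v 45%, latent correlation 0.3 to 0.8.**

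| Baseline prevalence | Power, change | Power, common baseline | Loss (points) |
|---|---|---|---|
| 50% | 55–81% | 76–89% | 8–21 |
| 70% | 50–74% | 75–88% | 14–25 |
| 80% | 45–64% | 77–85% | 21–32 |
| 90% | 29–37% | 75–80% | 43–46 |
| 95% | 15–19% | 75–77% | 58–60 |

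At 95%, about 13% of runs had an arm at 0% or 100%, where the logit contrast cannot be estimated. With an identity link the loss runs from about 24 points (50% baseline, low correlation) to about 1 point (95% baseline).

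**Second set of assumptions.** Fitted GEE models (logit, exchangeable, robust SE, 50% v 25% at 6 months) gave 62% v 81% at 50% baseline (phi about 0.34), 82% v 90% at 50% (phi about 0.59) and 56% v 81% at 80% (phi about 0.39).

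**Type I error.** In the fitted GEE models the null rejection rate was 4.7–5.3% for the change contrast and 4.3–5.0% for the common-baseline contrast.

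**The case against.** The strongest reply is that the article names a contrast, not a parameterization. A model without a baseline arm term also describes change, from a shared starting level, and a fuller analysis plan could specify exactly that. This stands in part: the text does not rule out the better model. But the wording points to the ordinary interaction, nothing in the article holds baseline common, and the improvement needs only a baseline already collected.

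Four stronger readings are tempting and are not supported:
- *The plan answers a different question.* It does not. With a true baseline difference of zero, both contrasts estimate the same 6-month difference on the link scale. The issue is efficiency.
- *The test is invalid.* Type I error is held.
- *The plan loses 20 points of power.* That depends on link, baseline prevalence and correlation, none of which the article gives. At mid-range baseline prevalence with high correlation the loss is about 8 points. With an identity link and very high baseline prevalence it is nearly nil.
- *The three points might be 3, 6 and 12 months, so that a sustained early effect gives no difference in change.* Table 1 does collect the mobility items at 12 months, but the Design section describes three measurements, "at baseline immediately after discharge from hospital, and at three and six months thereafter", and that is the reading to use.

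It is also fair that the article does not say which multi-category items are dichotomized for GEE, and that its sections disagree on whether self-reported mobility is primary.

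**Conclusion.** The point holds as one of efficiency. On the natural reading, the stated contrast spends power on estimating a baseline arm difference that randomization has already set to zero in expectation. With 53 evaluable per arm and an assumed 70% v 45% at 6 months, the loss is about 8 to 21 points on the logit scale at 50% baseline prevalence and about 20 to 30 points or more at 80% and above. With an identity link it ranges from about 24 points to 1. These figures are conditional on assumptions and do not predict this trial's power. The direction is firm: in every setting examined, the common-baseline or baseline-adjusted analysis had the higher power. The accelerometer and SPPB analyses are not touched by this point.

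**What to change.** Keep GEE and replace the stated contrast with the arm difference in prevalence at 3 and 6 months, fitted in one of two ways:
- baseline, 3 and 6 months as outcomes, with visit effects and arm-by-follow-up-visit terms but no baseline arm term; or
- 3 and 6 months only as outcomes, with the baseline value of the same item as a covariate.

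The first keeps a marginal effect. With a logit link the second gives an odds ratio conditional on baseline, so the report should say which is used. In the first form an exchangeable or unstructured working correlation lets baseline add precision. Under working independence the estimate is simply the follow-up difference, which had 73% power in the worked logit case and so still recovers most of the loss.

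The cost is one sentence of analysis text and no new data. The result is no longer presented as a group-by-time interaction. Observed baseline prevalences can still be tabulated by arm.
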